### Concealed allocation

The trial statistician (AS) will be responsible for generating the random allocation sequence using R (R Core Team and the R Foundation for Statistical Computing) (
R-Project, 2022). The six clusters (plus two reserve clusters) will be randomised into two trial arms, or blocks (intervention and control). Thus, each site will be randomly assigned to one arm of the trial, ensuring an equal number of clusters in each arm. In addition, two sites will be randomly assigned into each arm as additional reserve sites. A member of the research team will be responsible for informing participants of their allocation and maintaining an undisclosed record of each cluster's allocation in line with recommendations (
Eldridge *et al.*, 2016). To minimise expectation bias, the personnel involved in recruitment (such as GPs, clinicians or local champion), assessment and analysis of the quantitative data will be blind to cluster allocation. Concealed allocation procedure will be followed, detailed and monitored. Only the relevant people will have access to the allocation data, which will be secured, and password protected.

### Music and Movement for Health Programme

The use of theory in intervention development is crucial to increase intervention effectiveness and facilitate behaviour change (
Aunger & Curtis, 2016;
Fernandez *et al.*, 2019). As such, the programme and its mode of delivery have been designed following the Medical Research Council (MRC) guidance on developing complex interventions (
O'Cathain *et al.*, 2019) and guided by the Multi-level Leisure Mechanisms Framework (
Fancourt *et al.*, 2021). The intervention development process included: (1) reviewing published research evidence and examining existing protocols for facilitating music, singing and dance groups with older people in the community, (2) drawing on existing theories and techniques to facilitate participation and behavioural change including Social Cognitive Theory (
Bandura, 1998;
Kelder *et al.*, 2015) and Self Determination Theory (
Deci & Ryan, 2004), as the research demonstrates the integration of multiple theories can effectively facilitate physical activity engagement with older adults and 3) involving stakeholders through PPI panel feedback and TEC stakeholder consultation workshops. In addition, the programme will include co-design with the participants to tailor the programme to each community group. The Multi-level Leisure Mechanisms Framework was used to support the design of a more holistic, theory driven, and cross-disciplinary intervention. The framework emphasises the key underlying processes including psychological, biological, social, behavioural, and health behaviour at play when promoting health (
Fancourt *et al.*, 2021), and highlights the potential mechanisms that could link the
*Music and Movement for Health* project to wider health outcomes.

The
*Music and Movement for Health* intervention was systematically designed for community-dwelling older adults who are ≥65 years old. It consists of 12 weeks of 1.5 hours weekly supervised session at a local community centre (considering ease of access, parking and amenities) and 1 hour (3x 20 Minutes) home-based programme combining moving to music and singing. The warm-up, cool down and dances were informed by evidence from dance studies (
Clifford *et al.*, 2022) and effective falls prevention programmes, including the Otago and ‘LiFE Study’ programmes (
Campbell & Robertson, 2003;
Clemson *et al.*, 2012). The exercise and dance components of the programme will be tailored and progressed in line with ability and preferences of the participants for example movements performed while seated, using chair support or unsupported. The music therapy component of the intervention was informed by key studies in the area on effective programmes for older adults. The time of the intervention will be either late morning or early afternoon (
Moss *et al.*, 2022). The
*Music and Movement for Health* intervention for this study will be facilitated by a dance teacher, music therapist, and physiotherapist over 12 weeks. Each session over the course of the 12-week intervention will be structured to include a warm-up, music, singing and dance, creative response, followed by a cool-down a social tea and chat where participants will be encouraged to ask questions, provide feedback. Behavioural Change Techniques will be used encourage participants incorporate music and dance into daily activity (
French *et al.*, 2014), as the health promotion research demonstrates that employing theory-based methods increases intervention effectiveness in changing behaviour (
Fisher *et al.*, 2002;
Van Achterberg *et al.*, 2011). A playlist of participant’s personalised music will be developed in conjunction with the programme to facilitate participation in a home programme, whereby participants will be asked to perform the exercises to music. Home programme completion will be monitored using a self-report daily log. All participants will be advised to report any adverse effects and safety will be monitored during the sessions.

### Control group

The control group will be a true control usual care comparison group of participants. However, this group will be offered the chance to participate in the arts-based programme for six weeks at the end of data collection if they desire. Participants will be asked to complete a falls log and continue with any usual concomitant care. However, people will be advised not to take up any new physical activity that includes dancing and/or music, which could have a confounding effect on the outcomes of the trial. Individuals will discontinue in the programme if they develop any severe adverse events during the study which may or may not be related to the programme and would affect a participant’s ability to participate in the programme safely (such as chest pain or an injurious fall). In the case of a participant developing a severe adverse event they would require further medical investigation and GP clearance to continue their participation. Participants can also choose to discontinue with the programme at any time for any reason. A summary of the study design can be found in
Figure 2.

**Figure 2. f2:**
[figure not shown]
Graphical method for depicting randomised trials of complex programmes (
Perera *et al.*, 2007).

### Assessment procedures

Participants will be screened and assessed at baseline and at follow-up after the 12-week programme by blinded assessors. Following several trial runs, it is estimated that it will take approximately 60–70 minutes to complete the baseline assessments and around 40–50 minutes to complete the follow-up assessments. To avoid fatigue, the assessments will be distributed across four to five stations with a range of different assessments at each station at each assessment session. This will enable physical performance measures to alternate with more sedentary questionnaire measures. In addition, a dedicated refreshment station will be in place for participants to take a break whenever needed during the assessment.

At baseline, demographic characteristics including participant’s age, gender, ethnicity, number of years in education, living status, number of people living in the participant’s house, co-morbidities, number of medications, health service usage, falls history in the previous twelve months, and past dance experience and music experience will be recorded. Eligible participants that consent to participate will be advised not to change their exercise habits and to inform the research team of any changes made to their medical or exercise regime during the study. Feasibility of the programme will be assessed quantitatively by reporting:

Recruitment rates: will be assessed by reporting the recruitment rate (as the number of participants recruited and randomised per centre per month and the number of people enrolled over the number of people who expressed an interest in taking part). Refusal rates will also be documented where provided.Retention: proportion of individuals who after enrolment completed the baseline and follow-up assessments. We will record numbers who completed baseline and assessment at 12-week follow-up and attendance at programme. We will calculate the minimum outcome assessment target, which is set at a retention rate of at least 80% of recruited participants with valid baseline and 12-week primary outcome data i.e., less than 20% attrition at outcome assessments at baseline and follow-up.Attendance at supervised sessions: We will record the percentage of participants that attend the supervised sessions (adherence). Minimum average attendance target will be determined as the minimum average attendance by recruited participants set as 65%.Participation in home exercise programme: Using a self-complete calendar we will record how many participants (and how often) they engage in the home exercise programme.Safety will be assessed through self-report of direct or unrelated adverse events (e.g., falls or pain during the programme period). Falls: A falls diary (Appendix 7) will be completed. Participants or a nominated family member/career will receive a weekly reminder to complete the log. Completing a falls diary encourages recall, identifies the key circumstances surrounding falls and their content focuses the programme. The falls diary will include: Date and time of fall; location of fall; what caused the fall; type of injury sustained; and action taken. The falls diary is more accurate than retrospective recall over varying time periods.

The variability, consistency, response rates and data completeness for each of the secondary outcome measures will be determined. The secondary outcomes of the study have been used in previous studies with older adults, have undergone psychometric testing and include:

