**Figure 1. f1:**
[figure not shown]
The Pragmatic-Explanatory Continuum Indicator Summary 2 (PRECIS-2) wheel-Music and Movement for Health (
Loudon *et al.*, 2015). This figure is an original figure produced by the authors for this article.

As evident in
Figure 1, a broad consultative approach was used to ensure our eligibility criteria are appropriate, representative, and inclusive; and exclusion is aligned with usual care considerations. We will use a variety of recruitment strategies and envisage that most of the participants will be recruited via usual pathways, including social prescription by professionals as well as advocacy groups, newspapers and social media. The setting is both community and home based and not a controlled environment. Qualified dance teachers and music therapists will deliver the arts-based programme to participants randomised to receive the programme. The programme will be designed so that it can be integrated and implemented into the community setting. As such, the programme could easily occur in the community without the extensive use of resources. The
*Music and Movement for Health* study contains key ingredients to ensure fidelity in content and delivery but sufficiently flexible to accommodate preferences, skill level and the needs and abilities of the various community cohorts. We are not introducing special measures to incentivise compliance. However, we will monitor participation using a log and include behavioural change techniques (BCTs) to optimise participation in the programme (
Kok *et al.*, 2016). Our primary outcomes are feasibility and acceptability, which are relevant to inform a future definitive trial and the secondary outcomes are relevant to the participants. Our analysis will include data from participants in both intervention and control groups regardless of their level of engagement during the intervention.

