### Sample size

As our primary outcomes are feasibility it is desirable to keep the sample size small enough to allow close monitoring of participants and the programme while large enough to obtain sufficient data on our primary outcomes of feasibility. For feasibility reasons we will ensure we have sufficient numbers in each group to generate a ‘group’ climate likely to maximise adherence. Hence if the group gets too small, it becomes unviable for participant engagement and sense of community. The minimum numbers required to sustain a community-based music and movement programme and maintain the required group dynamics is between 10–12 older adults per group; guided by practice expertise within the research team and previous feasibility studies (
Clifford *et al.*, 2021;
O’Regan *et al.*, 2020). The primary feasibility outcomes will be evaluated by assessing recruitment rates (the rate of participants recruited to the study); retention rate (the number of participants who complete measures at baseline and at follow up post intervention) and minimum average attendance (number of participants who attended at least 65% of the intervention sessions). Hence, we aim to recruit a minimum of 72 participants in total (n=12 per cluster) allowing for 20% attrition (n=60; n=10 per cluster), we will be able to estimate a recruitment rate of 60% within a 95% confidence interval +/- 12.6%; a retention rate of 80% within a 95% confidence interval of +/- 10.3% and a minimum average attendance of 65% within a 95% confidence interval of +/- 12.3%. 

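### The primary attendance outcome has two incompatible definitions under one name, and its stated precision counts people from both arms although only the intervention arm has sessions

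*Protocol article*

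**What the plan says.** The Abstract and the Sample size section name recruitment, retention and minimum average attendance as the primary feasibility outcomes. Attendance is then described in several ways.

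- Sample size: "minimum average attendance (number of participants who attended at least 65% of the intervention sessions". This counts people over a per-person threshold. Table 1 repeats it in the column of feasibility criteria. Neither place says what number or share would be enough.
- Assessment procedures: "Minimum average attendance target will be determined as the minimum average attendance by recruited participants set as 65" per cent. This is a target for a mean.
- Assessment procedures, in the preceding sentence: "We will record the percentage of participants that attend the supervised sessions (adherence". This is a percentage of people, with no session threshold.
- Sample size, precision statement: "a minimum average attendance of 65% within a 95% confidence interval of +/- 12.3" per cent. Here 65% is the value being estimated.

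On retention, Assessment procedures and Table 1 set the target as "a retention rate of at least 80% of recruited participants with valid baseline and 12-week primary outcome data". The paragraph under Figure 1 says "Our primary outcomes are feasibility and acceptability, which are relevant to inform a future definitive trial", and the Abstract lists the clinical measures as secondary.

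**The concern.** A mean attendance and a proportion of people above an attendance threshold are different quantities. The same 65% serves as the per-person cut-off, the target mean and the anticipated share, so a reader cannot tell which result is to be compared with it. Attendance helps decide whether a definitive trial goes ahead. If the definition is left open, it can be settled after the attendance logs have been seen. The precision statement has a related fault: it fits only the share definition, and its sample size cannot be reached by an outcome that exists in one arm.

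**Working it through.** **Inputs.** Six clusters of 12, 72 recruited, 20% attrition allowed, 60 (10 per cluster) given as remaining (Sample size). Clusters allocated 1:1 (Randomisation), so the intervention arm has 3 × 12 = 36 enrolled, or 3 × 10 = 30 after attrition. Twelve weekly supervised sessions (Music and Movement for Health Programme). Since 0.65 × 12 = 7.8, the per-person threshold is met at 8 sessions.

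**1. Reproducing the stated margins.** The formula is 1.96 × √(p(1 − p)/n), and 72 × 0.8 = 57.6, rounded to 58.

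| Rate | Stated margin | n = 58 | n = 60 | n = 72 |
|---|---|---|---|---|
| Recruitment 60% | 12.6 | 12.61 | 12.40 | 11.32 |
| Retention 80% | 10.3 | 10.29 | 10.12 | 9.24 |
| Attendance 65% | 12.3 | 12.28 | 12.07 | 11.02 |

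All three stated figures match n = 58. With n = 60 and a t multiplier the margins are 12.66, 10.33 and 12.32, so the last two also match on rounding. On either route the attendance margin is a binomial calculation on both arms together. It therefore fits the share definition and not the mean.

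**2. The margin on the arm that has sessions.** Controls are offered the programme only after data collection (Control group).

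- n = 36: 1.96 × √(0.65 × 0.35/36) = 15.6 points
- n = 30: 1.96 × √(0.65 × 0.35/30) = 17.1 points

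Neither allows for clustering.

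**3. How far the two measures can diverge, with 36 people.**

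| Pattern | Mean attendance | Share attending ≥ 8 of 12 |
|---|---|---|
| 20 attend 11, 16 attend 4 | (220 + 64)/432 = 65.7% | 20/36 = 55.6% |
| 24 attend 8, 12 attend 2 | (192 + 24)/432 = 50.0% | 24/36 = 66.7% |

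No clumping is needed for a gap. If everyone independently had a 65% chance of attending each session, the probability of reaching 8 of 12 would be 0.583. A true mean exactly on target would then correspond to an expected share of about 58%.

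**4. How often verdicts would differ.** This step assumes a 65% pass mark for both measures, 36 people, and beta-binomial attendance with within-person correlation between 0.1 and 0.5. In simulation the verdicts disagree in about 27% to 41% of trials when true mean attendance is 65% to 70%, and in about 6% to 16% when it is 60% or 75%.

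**5. Retention.** Every measure taken at both visits is labelled secondary, so the reference to primary outcome data names no measurement. The same item in Assessment procedures, however, defines retention as completing the baseline and follow-up assessments, and glosses the target as attrition below 20% at those assessments.

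**The case against.** Four things can fairly be said on the other side.

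First, only one numeric attendance target is stated, the 65% mean. The share has no pass mark, and the 65% in the precision statement is a planning value, beside a 60% recruitment rate that is likewise not set as a target. A reader might infer that the protocol holds two rules under which the same data both pass and fail. The documents do not support that. They hold two definitions, one without a threshold, and an opposite verdict needs an assumed pass mark. This stands, and the missing mark is part of the defect.

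Second, a reader might infer that retention cannot be assessed because no primary outcome data exist. That does not hold, because the completion rule in Assessment procedures is workable. What remains is loose wording, repeated in Table 1 without the gloss.

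Third, the reference to recruited participants could be read as counting controls as non-attenders. That reading is implausible: the item concerns supervised sessions, which controls do not have during the trial. The both-arm base of the stated margin is a separate matter, and that problem remains.

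Fourth, the Data analysis section confines the study to description and interval estimation, safety and acceptability also have criteria, and both attendance summaries come from the same logs. This limits the damage. It does not settle which summary is the criterion. The patterns in step 3 are constructed, and the simulated disagreement is large only near the target, though that is where a criterion has to decide.

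**Conclusion.** The point holds as a contradiction in the text about a primary feasibility outcome. A later analysis plan could choose one definition, but would then depart from at least one of these published statements. Two parts rest on the documents alone: the term has two incompatible meanings, and the 12.3-point margin needs about 58 people where about 36 are available, giving about 15.6 points (17.1 with 30) before clustering. The divergence of 10 to 17 percentage points in the two examples is arithmetic on illustrative patterns. Describing those as opposite verdicts assumes that 65% is also the pass mark for the share, which the protocol does not say. The retention wording is a minor correction.

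**What to change.** Use one attendance definition for the feasibility criterion in Sample size, Assessment procedures and Table 1. The denominator should be all participants enrolled in intervention clusters, with drop-outs counted as absent, and the pass mark should be explicit. Report the other measure descriptively. Either choice is defensible:

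- **Keep the mean.** Retain the 65% target and change the definitions in Sample size and Table 1. Remove the binomial margin, or replace it with a margin for a mean, which needs an assumed between-person standard deviation that the article does not give.
- **Keep the share.** Define it as the proportion attending at least 8 of 12 sessions, give it a pass mark, change Assessment procedures, and restate the margin for the intervention arm: about 15.6 points with 36 or 17.1 with 30, before clustering.

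In the retention target in Assessment procedures and Table 1, replace the reference to primary outcome data with the completion rule already given: baseline and 12-week assessments completed by at least 80% of all enrolled.

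The cost is wording in three places and one margin restated or removed. No new data are needed, because session attendance logs are already planned under Process evaluation.

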### Physical performance measures

Timed Up and Go Test (TUG): The aim of the TUG is to assess functional mobility and balance while performing a sequence of functional tasks. It is a simple, valid, reliable and cost-effective measure to re-produce in a clinical setting as it requires the participant to stand up from a chair, walk three meters, turn around and walk back to sit on the chair again. TUG scores are associated with future falls in older adults, TUG time ≥12.6 seconds (adjusted for age, gender, comorbidities, medications, and past history of two falls) was significantly associated with future falls (
Kojima *et al.*, 2015).TUG-Cognitive (Dual Task Ability): The TUG-Cognitive will be used to measure dual task performance during the TUG. The time to complete the test is used to score dual task performance with faster times indicating better performance. This test has high criterion validity and very good test retest reliability (
Hofheinz & Schusterschitz, 2010).The 30 Second Sit to Stand Test, also known as the 30 second chair stand test (30CST), assesses the lower extremity strength and endurance in community-dwelling older adults. The test provides a reasonably reliable and valid indicator of lower body strength in generally active older adults (
Rikli & Jones, 1999).Single Leg Stance Test is a measure of static postural control. This test requires participants to stand on one leg with their hands on their hips, unaided. The time is tracked for 30 seconds. Higher scores indicate better postural control. Scores of under five seconds are suggestive of greater postural deficiencies (
Jonsson *et al.,*, 2004). Excellent reliability has been found for this test (ICC 0.99) (
Springer *et al.,* 2007).Short physical performance battery (SPPB): The SPPB measures lower limb function including strength, endurance, gait, and balance through three components, walking speed, chair stands, and standing balance. The SPPB is able to predict mortality and functional mobility limitations in older adults (
Treacy & Hassett, 2018). Scores range from 0 to 4 (0= inability to complete the task; 4= highest level of function) for each task of SPPB with the sum of these three tests (0–12) reflecting the complete measurement of physical function.

